**Secondary outcomes**

*Mortality.* Analysis will follow standard methods in other clinical trials for malaria[64, 81, 82]. Mortality at 48 h and 14 days will be coded as a binary variable. Absolute and relative risk reduction will be reported with binomial 95% confidence intervals. Analysis will be by chi-squared test or Fisher exact test if the expected number of deaths is less than five in one or both treatment groups. In addition, we will present Kaplan-Meier survival curves comparing patients treated with iNO compared to placebo.

Time to death will be analysed using survival analysis (Cox proportional hazard model for difference between treatment arms).

*Time to recovery.* Among survivors (subgroup analysis of randomized participants), recovery times will be analysed by survival analysis (Cox proportional hazard model for difference between treatment arms). Time to sit unsupported, time to coma resolution (in the subset of patients with coma at study admission) and time to discharge will be documented by treating clinicians (blinded to intervention). Time to fever resolution, defined as the time required to achieve a temperature  $<38^{\circ}\text{C}$  and the time to maintenance of temperature  $<38^{\circ}\text{C}$ , will be determined from frequent vital sign monitoring. The time required to achieve a reduction in parasite density of 50%, 90% and to undetectable levels will be determined from daily blood smears. Results will be expressed as the median time to each event, with 95% confidence intervals.

*Additional biomarkers* (continuous variables, multiple measurements longitudinally collected) will be analysed using mixed-effects linear models, with the raw value or log-transformed value of the biomarker level as the dependent variable, as appropriate.

*Neurocognitive outcomes.* Statistical analysis of neurocognitive outcomes will be performed as follows. Frequencies of overall cognitive and neurologic deficits in children treated with iNO and children receiving placebo will be compared by  $X^2$  test or Fisher's exact test. Differences in cognitive areas affected in the two age groups (18 mo-4 years, 5-10 years) will be assessed by comparing frequency of individuals with deficits in each area by  $X^2$  test or Fisher's exact test. This will also serve as the best surrogate of level of impairment in a particular area in one age group vs another, since the type of testing for each cognitive area will be different for the two age groups, so no direct comparison of level of impairment will be possible across age groups. For individual tests, age-adjusted z-scores (determined from normative data in previous studies among healthy community controls) will be analyzed by means of mixed-effects models to examine study group differences in relation to neurocognitive outcomes. The models will provide estimated mean differences between children treated with iNO to placebo controls.

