## **4 TRIAL DESIGN**

### **4.1 Endpoints**

*Primary endpoint:* Daily rate of change of Ang-2

*Secondary endpoints:*

1. Clinical efficacy:
  - a. 48 hour and 14-day mortality
  - b. recovery times:
    - i. time to fever resolution
    - ii. time to sit unsupported
    - iii. time to hospital discharge
  - c. time to parasite clearance
  - d. incidence of recrudescence at day 14

2. Other biomarkers and genetic determinants of malaria disease severity
  - a. whole blood lactate level
  - b. biomarkers and genetic determinants of endothelial activation, inflammation and coagulopathy, to be determined
3. Neurocognitive outcome at 6 months after discharge

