#### *Biomarkers and genetic determinants of disease severity*

Lactate is produced by the anaerobic metabolism of glucose in the absence of adequate tissue oxygenation. As such, elevated lactate levels represent a final common pathway of tissue hypoxia and decompensated shock, the forerunner of cardiovascular collapse and death. Lactate levels at presentation predict pediatric mortality in a wide variety of clinical conditions including malaria[83, 84], sepsis[85], pediatric trauma[86] and cardiac disease[87]. We will measure lactate as an independent biomarker of disease severity during the clinical trial.

Biomarkers and genetic determinants of severe malaria pathogenesis may provide additional insight into the pathways and processes altered in cerebral malaria and affected by iNO delivery. We plan to examine biomarkers of endothelial activation, inflammation including cytokines, and coagulopathy which are central to the pathophysiology of severe malaria. In addition, genetic pathways involved in severe malaria and response to iNO will be investigated.

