### **4.3 Description of measures taken to minimize bias**

#### **(a) Randomization**

##### ***Sequence generation***

A computer generated randomization list will be created. Simple randomization will be used. Important prognostic variables including patient age, disease severity, and HIV seropositivity will thus be expected to be distributed randomly between treatment arms.

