***Whole blood lactate level***

A handheld lactate meter will be used by medical officers to document whole blood lactate levels at each blood draw. The CRF will record the lactate levels, the time of collection, and any difficulties that may compromise the validity of the data.

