## **5.2 Exclusion criteria**

1. Baseline methemoglobinemia (>2%)
2. Known renal, cardiac, or hepatic disease or other chronic illnesses like diabetes, epilepsy, cerebral palsy, clinical AIDS, suspected or known hemoglobinopathy (e.g., sickle cell anemia, G6PD deficiency).
3. Suspected bacterial meningitis.
4. Patient already received parenteral quinine in the ED prior to eligibility assessment.
5. Patient unlikely to tolerate delivery mask for more than 24 hours.
6. Severe malnutrition
7. Severe malarial anemia (Hb <50g/L) without other signs of severe malaria.

---

 repeated seizures (two or more generalized seizures in 24 h); prostration (in children 1 year and older, the child is unable to sit unsupported or stand although was able to before the illness; impaired consciousness (Blantyre Coma Score <5 in children 1 to 4 years, GCS <14 for children ≥ 5 years); respiratory distress: sustained nasal flaring, deep breathing or intercostal/subcostal retractions.

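### Mortality is compared without adjusting for entry lactate, a collected baseline value the protocol calls predictive of death; the tests are valid, but some efficiency is given up

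*Protocol*

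**What the plan says.** Section 4.1 lists "48 hour and 14-day mortality" first among the clinical efficacy endpoints, all of them secondary. For the binary outcomes, Section 9.1 states: "Analysis will be by chi-squared test or Fisher exact test if the expected number of deaths is less than five". That threshold is applied to either arm, and absolute and relative risk reductions are to be reported with binomial confidence intervals. For the time scale it states: "Time to death will be analysed using survival analysis (Cox proportional hazard model for difference between treatment arms"). No baseline covariate is named for either analysis.

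On lactate, Section 4.1 (biomarkers) states: "Lactate levels at presentation predict pediatric mortality in a wide variety of clinical conditions including malaria". Section 4.9 lists lactate in the study-entry blood work and adds: "A handheld lactate meter will be used by medical officers to document whole blood lactate levels at each blood draw".

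Consciousness is assessed for eligibility. The footnote to the inclusion criteria gives "impaired consciousness (Blantyre Coma Score <5 in children 1 to 4 years, GCS <14 for children ≥ 5 years") as one of several qualifying features.

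On allocation, Section 4.3(a) states: "Simple randomization will be used". It expects disease severity to be distributed at random between the arms. Sections 9.1 and 9.7 use other prognostic variables only to define subgroups. Section 9.6 says that departures from the protocol's planned analyses will be reported as post hoc and exploratory.

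**The concern.** Few deaths are expected, so the mortality comparison will be imprecise. A baseline variable that predicts death explains part of the outcome. Leaving it out of the analysis gives up power and precision that could be had from data already collected. Neither stratification nor adjustment takes up the part of the arm difference that comes from chance differences in severity.

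A smaller point goes with it. Mortality is tested at 48 hours, at 14 days and by the Cox model, all at the 0.05 level of Section 9.3, and none is named as deciding. Section 9.5 makes a sensitivity analysis depend on a significant mortality benefit without saying which test has to show it.

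The timing of the fix also matters. Under Section 9.6, an adjusted analysis added later could be classed as post hoc.

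**Working it through.** **Inputs from the protocol.** 180 children, about 90 per arm (Section 9.2); about 20% mortality under standard care (Section 8.1), with 6 to 29% in the trials reviewed in Appendix 1; alpha 0.05 (Section 9.3), two-sided as in Section 9.2.

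**Assumptions, because the protocol gives no figure.** Mortality on iNO of 14%, 10%, 6% or 4%. One normally distributed baseline score with a c-statistic for death of 0.65 to 0.90. No losses; the protocol's 10% allowance would leave 90 × 0.9 = 81 per arm and lower every power figure below.

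**The plan's own figure.** There is none to reproduce. Section 9.2 sizes the trial on Ang-2 only and states no mortality effect or power.

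**Expected deaths.** With no effect: 180 × 0.20 = 36. With deaths halved on iNO: 90 × 0.20 + 90 × 0.10 = 27.

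**Unadjusted power, binary test.** Power = Φ{[|p1 − p2|√n − 1.96√(2p̄(1 − p̄))] / √(p1(1 − p1) + p2(1 − p2))}. For 20% vs 10%, p̄ = 0.15: [0.10 × 9.487 − 1.96 × 0.505] / 0.500 = −0.082, so power is 47%. The same formula gives 19% for 20% vs 14% and 80% for 20% vs 6%.

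**Unadjusted power, Cox model.** For 20% vs 10%, the hazard ratio is ln 0.90 / ln 0.80 = 0.472 with 27 deaths. Φ(√27/2 × 0.750 − 1.96) = Φ(−0.01), about 50%.

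**Adjusted logistic regression against chi-squared.** Simulation with 4,000 replicates per cell and a likelihood-ratio test. Entries are gains in power points:

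| Deaths, control vs iNO | c = 0.65 | 0.70 | 0.75 | 0.80 | 0.85 | 0.90 |
|---|---|---|---|---|---|---|
| 20% vs 14% | 1.3 | 2.5 | 2.5 | 4.0 | 6.5 | 10.5 |
| 20% vs 10% | 2.2 | 4.4 | 7.0 | 9.2 | 12.4 | 20.0 |
| 20% vs 6% | 1.5 | 2.8 | 4.2 | 5.9 | 9.8 | 13.7 |
| 20% vs 4% | 0.5 | 1.1 | 1.6 | 2.8 | 3.7 | 4.8 |

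For 20% vs 10% and c from 0.65 to 0.85, adjusted power runs from 49% to 61%, against 45 to 49% unadjusted in the same simulated trials. With no treatment effect, the rejection rate was 4.4 to 5.3% for chi-squared and 5.0 to 5.7% for the adjusted test.

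**Adjusted Cox model against arm-only Cox model.** 2,000 replicates, c from 0.65 to 0.85. Gains were about 1 to 9 points for 20% vs 14%, 2 to 18 for 20% vs 10%, and 2 to 10 for 20% vs 6%. At lower control mortality (10% vs 5%) they were about 0 to 6.

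**Chance imbalance.** The probability that a baseline score differs between arms by more than 0.2 SD is 2 × [1 − Φ(0.2/√(2/90))] = 2 × [1 − Φ(1.34)] = 18%.

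**Three mortality tests.** With no effect, simulation puts the chance that at least one of the 48-hour, 14-day and Cox tests is significant at about 6.5 to 9%, depending on the assumed share of deaths in the first 48 hours.

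**The case against.** Unadjusted comparisons of randomised arms are standard and hold their type I error, and Section 9.1 says it follows earlier malaria trials. Covariates for a secondary endpoint are often left to a statistical analysis plan, and one may exist here. The Cox sentence describes the contrast of interest and does not expressly exclude covariates. Even after adjustment, power for halving deaths is modest. All of this stands, and it keeps the point small. It does not remove the point: Section 9.1 positively specifies the unadjusted binary test, and Section 9.6 could turn a later adjusted analysis into an exploratory one.

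Three stronger readings are tempting, and the protocol supports none of them.

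- A reader might infer a fixed loss, such as 5 to 15 points. That needs both a particular mortality effect and a strongly prognostic score, and the protocol gives neither. At a c-statistic of 0.70 or less, the gain was under 5 points for every effect tried.
- A reader might infer that simple randomisation lets severity bias the result. An 18% chance of a 0.2 SD difference is ordinary for simple randomisation at this size, and the nominal 5% error rate already allows for it. It is imprecision, not bias.
- A reader might put coma score on the same footing as lactate. It is an eligibility feature on two age-specific scales, Section 4.9 does not name it as a case report form item, and the protocol does not say that it predicts death. Lactate is the firmer covariate.

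On the three tests, they are highly correlated and concern a secondary endpoint, so the inflation is modest. The worst-case rule in Section 9.5 guards against missing outcomes, not against choosing among tests.

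**Conclusion.** The mortality analysis is valid but less efficient than the collected data allow. With 90 per arm, 20% control mortality and deaths halved, adjusting for one baseline score adds about 2 to 12 power points in a logistic model for c-statistics of 0.65 to 0.85. Over the wider assumptions tried, the gain runs from under 1 to 20 points. These figures depend on an assumed treatment effect and on how well entry lactate predicts death in these children. Adjusted power for a halving of deaths stays at about 50 to 60% (logistic), so the endpoint remains underpowered either way. This is a worthwhile low-cost improvement, not the correction of an error. The lack of a named deciding mortality test is a minor companion point.

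**What to change.** In Section 9.1, name one deciding mortality analysis in advance. An example is 14-day mortality by logistic regression on treatment arm and entry lactate on the log scale, optionally with impaired consciousness at entry as yes or no by the age-appropriate scale in the eligibility footnote. From that model, report standardised absolute and relative risk reductions with confidence intervals, so that the effect measures the protocol promises are kept.

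Add no further covariates. With 27 to 36 deaths, the three terms (arm, lactate, consciousness) leave 27/3 = 9 to 36/3 = 12 deaths per term.

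Adjust the Cox model for the same covariates as a supporting analysis. Keep the unadjusted tests and 48-hour mortality as supportive. Section 9.5 expects 48-hour mortality to be captured more completely than 14-day mortality, so the trial team may prefer it as the deciding time point. What matters is that one analysis is chosen in advance and that the trigger in Section 9.5 refers to it.

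The cost is a change of wording, a little more analysis work and a stated rule for missing entry lactate. Lactate needs no new data collection. If consciousness is used, confirm that the entry score is recorded on the case report form.

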***Primary outcome***

The daily change in Ang-2 over the hospital admission will be the primary efficacy outcome. Elevated Ang-2 levels are associated with poor clinical outcome in severe malaria[33, 34] and Ang-2 has been used to follow disease progression and recovery in previous studies of malaria[33]. Thus, Ang-2 is an objective, quantitative marker of disease severity, validated for longitudinal follow-up of patients with malaria. Ang-2 levels will be measured longitudinally at admission (day 0), day 1, day 2 and day 3 of hospital admission. In patients treated for severe malaria who survive the infection, Ang-2 levels have been shown to decrease linearly during recovery at a mean rate of 2700pg/mL per 24h[33].

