***Serious Adverse Event or Serious Adverse Drug Reaction***

*A serious adverse event (experience) or reaction is any untoward medical occurrence that at any dose:*

- *results in death,*
- *is life-threatening,*
- *requires prolongation of existing hospitalisation, or*
- *results in persistent or significant disability/incapacity*

In this trial of critically ill children hospitalized with severe malaria, mortality is expected to occur in approximately 20% of participants who receive standard medical care[90].

Monitoring serious adverse events during the trial is therefore complicated by the fact that death is part of the natural progression of disease, even under conditions of optimal clinical care (Uganda standard of care). We propose to monitor mortality continuously to detect variations above the baseline expected mortality rate, to allow for early implementation of corrective actions, if required.

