## **9.2 Number of subjects planned to be enrolled**

We will enrol 180 patients (approximately 90 in each treatment arm).

Based on a recent clinical trial of L-arginine as adjunctive treatment for severe malaria, among patients who subsequently recovered, Ang-2 decreased by 2700pg/mL/day (95%CI 1800-3600pg/mL/day)[33]. We assume that a 50% change in this parameter would represent a clinically significant therapeutic effect. By standard calculations for normally distributed data, 80 patients per group will provide 80% power to detect a difference between two treatment arms of 1350pg/mL/day at  $p=0.05$  (two-sided). This corresponds to a 50% difference in the rate of change of Ang-2 between the arms. To account for possible dropout, loss to follow-up, and/or non-evaluable data of 10% of patients, approximately 90 patients per study arm are required.

However, these calculations do not reflect the analytic plan. Therefore, a simulation study was performed. A number of assumptions needed to be made, such as within patient correlation and Ang-2 variability. Patient Ang-2 data were simulated using a

multivariate normal distribution. A simple autoregressive correlation structure was used with correlations of 0.75, 0.5 and 0.25 for lags 1, 2 and 3 respectively. In previous studies, variability appears proportional to the mean[33]. Simulations were run with three different relationships where the standard deviation was taken to be 40%, 50% and 80% of the Ang-2 mean at each time point. Both groups were assumed to start at Ang-2 levels of 15,000 pg/mL and the average values at each of days 1, 2 and 3 based on the hypothesized slopes of Ang-2. One thousand replications were performed at each standard deviation relationship and treatment effect. The mixed effects models were fit and the likelihood ratio test was used to test the hypothesis of no time by treatment interaction at the 5% level (two tailed). Table 4 shows the results of the power simulations.

Table 4: Power simulations for 90 patients per group

| Standard Deviation
(% of mean) | Slope Difference               |                                        |                                        |
|-------------------------------------------|---------------------------------------|----------------------------------------|----------------------------------------|

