### **9.5 Procedure for accounting for missing, unused, and spurious data**

**Primary endpoint.** The primary endpoint of this trial involves collection of four serial (daily) venous blood samples for the measurement of rate of change of Ang-2. Missing data may therefore arise for a number of reasons including: premature discontinuation of study gas (not tolerated, safety issues, caregiver or health provider discretion); mortality event prior to complete collection of samples; or patient dropout. Our primary analysis using a mixed-effects linear model takes into account all available data points, and is able to handle missing data.

**Secondary endpoints.** Mortality at 48 hours is expected to be captured relatively completely, whereas 14-day mortality may be subject to loss to follow-up. Patients with missing data will not be included in computation of mortality, and we will report the number of missing cases. In the event that a significant mortality benefit is observed, we will perform a sensitivity analysis wherein patients with missing data are assigned an outcome of death (iNO group) or alive (placebo group), in order to systematically bias results toward the placebo group. If significant differences remain in this analysis, the result will be considered robust to adjustment for missing data. Our alternative analysis using Kaplan-Meier survival curves will censor patients at the point of last contact, in the case of missing data.

For the time to recovery endpoints, missing data will be handled by censoring patients at the time of the last documented time point. For other continuous variables, missing cases will be excluded from the analysis (two-way repeated-measures ANOVA), or will not affect the analysis (mixed-effects linear model).

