## **9.7 Selection of subjects to be included in analyses**

All randomized subjects will be included in the primary *intention-to-treat* analysis (change of Ang-2 over time). A secondary *per-protocol* analysis may be performed

including only patients with evaluable data who received the study gas for the proscribed duration (72 hours).

HIV co-infection, co-existent bacteremia and/or meningitis, and blood transfusion may affect Ang-2 levels and may represent effect modifiers of iNO treatment. We expect that randomization and blinding will ensure relatively even distribution of these co-variables between treatment and control groups, although these co-variables may add unexplained variance (random error) in the dependent variable (Ang-2). We will therefore conduct a subgroup analysis of iNO effect among HIV negative patients without bacteremia who do not undergo blood transfusion, to examine the role of iNO in this carefully selected patient population. Additional subgroup analyses will be conducted according to other possibly important co-variables: age < 5 years or ≥5 years; cerebral malaria or other severe malaria syndrome (respiratory distress); HIV seropositivity; and severe anemia.

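### Recovery times are compared between arms in survivors only, which biases the comparison against the arm with fewer deaths

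*Protocol*

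**What the plan says.** Section 9.1 (Secondary outcomes, Time to recovery) states: "Among survivors (subgroup analysis of randomized participants), recovery times will be analysed by survival analysis", using a Cox model for the difference between arms. The same paragraph covers time to sit unsupported, coma resolution, discharge, fever resolution and reduction in parasite density. Section 9.1 plans no recovery comparison in all randomised children.

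Section 8.1 (Serious Adverse Event) says that "mortality is expected to occur in approximately 20% of participants who receive standard medical care". Section 4.1 lists mortality at 48 hours and 14 days as the first clinical efficacy endpoint, and section 9.1 analyses it separately.

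Section 9.5 says that for recovery times "missing data will be handled by censoring patients at the time of the last documented time point". For Ang-2 it names a "mortality event prior to complete collection of samples" among the causes of missing values and relies on a mixed model that "takes into account all available data points, and is able to handle missing data". Section 9.7 adds for that analysis: "All randomized subjects will be included in the primary" intention-to-treat analysis.

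**The concern.** A comparison of arms is protected by randomisation only if the analysis set is fixed at randomisation. Survivors are not such a set. If the treatment changes who survives, the two survivor groups differ in severity before any effect on recovery speed is considered. The arm with fewer deaths keeps children who would have died in the other arm, and these are likely to be slow to recover.

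The trial is set up in the hope that nitric oxide lowers mortality, so this is the case the analysis has to handle well. As written, a real survival benefit would push the hazard ratios for every recovery endpoint below 1, which would be read as slower recovery on nitric oxide.

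**Working it through.** **The plan's own figure.** The protocol gives no figure for recovery times. Its relevant figure is 20% expected mortality, or 0.20 × 90 = 18 deaths per arm. Appendix 1 works from the same value. With a threshold of 6 deaths in 10, P(6 or more of 10 at 20%) = 0.00637, so the average run length is 1/0.00637 = 157 inspections, as stated there.

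**Assumptions that are not in the protocol.** Recovery is exponential with a median of 36 h in children who would survive on either arm. Rescued children (dead on placebo, alive on nitric oxide) recover k = 2 or 3 times more slowly, with a median of 72 h or 108 h. Nobody else's recovery time changes. Placebo mortality is p0 = 20%, and mortality on nitric oxide is p1 = 10%, 15% or 20%.

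**Step 1, make-up of the survivor groups.** The share of rescued children among nitric oxide survivors is (p0 − p1)/(1 − p1). For p1 = 10% this is 0.10/0.90 = 11%, and for p1 = 15% it is 0.05/0.85 = 6%. Among placebo survivors it is zero.

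**Step 2, hazard ratio over time in survivors, p1 = 10%, k = 2.**
- At the start: (0.80 + 0.10/2)/0.90 = 0.94.
- At 72 h, 25% of the ordinary children and 50% of the rescued children have not recovered. The ratio is (0.80 × 0.25 + 0.10 × 0.50/2)/(0.80 × 0.25 + 0.10 × 0.50) = 0.225/0.250 = 0.90.
- At 144 h, the fractions are 6.25% and 25%. The ratio is (0.050 + 0.0125)/(0.050 + 0.025) = 0.83.

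The slow children make up a growing part of those still at risk, so the ratio drifts down.

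**Step 3, large-sample Cox hazard ratio** (score equation solved numerically over the whole course; above 1 means faster recovery on nitric oxide):

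| Mortality, placebo / nitric oxide | Survivors only, k = 2 to 3 | All randomised, deaths not recovered to day 14 |
|---|---|---|
| 20% / 10% | 0.91 to 0.85 | 1.24 to 1.21 |
| 20% / 15% | 0.95 to 0.91 | 1.11 to 1.10 |
| 20% / 20% | 1.00 | 1.00 |

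The true effect on recovery speed in children who survive on either arm is 1.00 in every row.

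**Step 4, a second model.** Here sicker children both recover more slowly and die more often (correlation 0.7 to 1.0), again with no effect on any child's own recovery time. The survivors-only hazard ratio is 0.87 to 0.95 at 10% mortality on nitric oxide and 0.92 to 0.98 at 15%. With 90 children per arm and 20% against 10% mortality, the planned analysis points against nitric oxide in 59 to 82% of trials. It is nominally significant in that direction in 5 to 15%, against 2.5% by chance.

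**Step 5, lower mortality.** Appendix 1 quotes 6 to 29% across earlier trials. In the model of Step 3, halving 10% mortality gives a survivors-only ratio of 0.95 to 0.92, and halving 6% gives 0.97 to 0.95.

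**The case against.** **These endpoints are secondary, and mortality is analysed in its own right.** This is true. The survivor restriction is also openly labelled a subgroup analysis, so a survival benefit would be reported beside the recovery times. That lowers the risk of misreading but does not correct the hazard ratios.

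**The size depends on assumptions.** This stands. The mortality reduction and the slower recovery of rescued children are not in the protocol, the bias shrinks at lower mortality, and it vanishes when mortality is equal.

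**The alternative answers a different question.** This stands in part. In the illustration the all-randomised ratio of 1.24 to 1.21 comes entirely from survival, so it does not measure speed of recovery. But the survivors-only ratio does not measure it either: it gives 0.91 to 0.85 where the true value among children who survive on either arm is 1.00.

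**Section 9.5 already censors missing recovery times.** This does not help. Children who die are outside the survivor set, and censoring them at death would treat them as if they could still recover like the others.

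**A stronger reading that the protocol does not support.** A reader might infer that the primary Ang-2 comparison can also be made to look harmful, because death is listed among the causes of missing values and "Elevated Ang-2 levels are associated with poor clinical outcome in severe malaria". But that analysis keeps all randomised children and all available values, including the day-0 sample. With the protocol's starting level, slope and correlations, and mortality falling from 20% to 10%:
- the bias is about zero (−11 to +7 pg/mL/day) if death depends only on Ang-2 already observed;
- it is 56 to 208 pg/mL/day, or 4 to 15% of the 1350 target, if death depends on the unobserved current value;
- it is 86 to 341 pg/mL/day, or 6 to 25%, if children who would die have flat or rising Ang-2.

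The third case reaches at most 468 pg/mL/day (35%) if mortality on nitric oxide is 5%. This would mainly dilute an effect of the planned size. A sensitivity analysis for it may well be in the statistical analysis plan, which is not shown.

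**Conclusion.** The point holds for the recovery-time endpoints. Section 9.1 fixes an analysis set that depends on a post-randomisation outcome the treatment is meant to improve. The comparison is biased against the arm with fewer deaths whenever the children saved are slower to recover. With 20% placebo mortality and the stated assumptions, a treatment with no effect on recovery speed shows a hazard ratio of about 0.91 to 0.85 if it halves deaths, and 0.95 to 0.91 if it prevents a quarter of them. The direction is the same in both models. The size rests on assumptions outside the protocol, and there is no bias if mortality is equal. With 90 per arm, a wrong-way estimate is much more likely than a significant false finding of harm.

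The point does not extend to the primary endpoint, for which the mixed model is acceptable.

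**What to change.** In section 9.1, make the between-arm recovery comparison in all randomised children, timed from randomisation, with death as a competing event. Children who die stay in the risk set as not recovered to day 14, analysed by cumulative incidence or a Fine-Gray model. Keep the survivors-only result beside it and call it descriptive. In section 9.5, limit censoring at the last documented time point to children not known to have died.

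The cost is wording only, since dates of death and recovery are already collected. The downside is that the all-randomised effect combines survival with speed of recovery. It must be labelled so and read beside the mortality results.

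The change belongs in the protocol: section 9.6 says that departures from the analyses described there are reported as post hoc and exploratory, so a later correction would lose standing.

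Optionally, add an Ang-2 sensitivity analysis that treats death before day 3 as a worst outcome. The mixed model stays primary.
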